## 3.4 Randomisation into four groups for the trial

When positive hookworm cases are identified through the prevalence survey, field workers will notify the students of "positive" results. These students will be requested to visit the school where they attend for participating in the trial. The field researchers will be formed by health personnel from the most accessible health centre IV or hospital-level health facility in Mayuge district: 1) Mayuge health centre IV located in Mayuge town council, 2) Kigandalo health centre IV located in Kigandalo sub-county, 3) Kityerera health centre IV located in Kityerera sub-county, and 4) Buluuba hospital in baitambogwe sub-county. The participants will be instructed to have a meal on the morning of the visit, following the protocol for taking fatty meal with albendazole as outlined in the study of Nagy *et al.*(25). These participants will be randomised into one group among four treatment options by applying the block randomisation method, stratified by health facility. The randomisation block size will be 8, and within each block there will be two participants allocated to each of the four trial arms. A randomisation list will be prepared beforehand using a random number generator. Each health facility will have its own random number list. The participants will take a meal four hours after the drug consumption to exclude the possibility of affecting albendazole absorption by immediate taking foods. But, water, no caffeine drinks, non-alcoholic beverages can be allowed during four hours fasting period.

Albendazole (AGOZOLE 400mg; batch number T11098, produced by AGOG Pharmaceutical Ltd., India) will be used for this trial. This is not a new drug. AGOZOLE albendazole is approved by the National Drug Authority (NDA) of Uganda and is widely available in the Ugandan domestic pharmaceutical market (NDA registered number: NDA/MAL/HDP/3013).

The trial is designed as an open-label randomised controlled trial with four arms:

Intervention group 1: participants will take 400mg of single-dose albendazole with 200 grams of avocado.

Intervention group 2: participants will take dual-dose albendazole without taking avocado. (Participants will take 400mg of single dose albendazole for two consecutive days)

Intervention group 3: participants will take dual-dose albendazole with 200 grams of avocado. (Participants will take 400mg of single dose albendazole with 200 grams of avocado for two consecutive days)

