**3.5.2 Stool sample collections**

Stool samples will be collected from enrolled students from the selected schools by the field workers who will visit the schools, and, as described above, from the students who take part in the albendazole treatment trial three weeks after treatment. The collected stool samples will be contained in a designated stool container secured in a cooling box carried by the field workers. The samples will be transferred to the laboratory and the Kato-Katz examination performed. Delivered stool containers will be secured in a refrigerator before being processed, and contained stools will be utilized for making slides with Kato-Katz method within 24 hours after being delivered to the laboratory.

- - 1. **Organizing laboratory examination**

The WHO recommends the Kato-Katz quantitative method as the standard methods for evaluating prevalence and intensity of soil-transmitted helminthiasis and schistosomiasis in endemic communities. Kigandalo health centre IV will be the base for parasitological examination since this health centre IV has the central laboratory of Mayuge district.

(Collection of stool samples)

Plastic stool containers and applicator sticks are provided in advance

1. Put stool (about 5g) into a plastic container.

2. Take stool to the school.

3. Keep stool in the container in the cooler boxes.

4. The cooler boxes contained stool samples are transported to Kigandolo HC IV for analysis in the afternoon of the same day.

5. Stool samples which are not treated with Kato-Katz method will be contained a refrigerator in the Kigandalo HC IV.

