**3.5.4 Parasitological examination for STH and schistosomiasis**

Kato-Katz procedure will be applied to prepare the slide for examination. Six South Korean professors of parasitology who participated in the prevalence survey in 2019 and the health specialist of Mayuge NTD Elimination project, will examine the prepared slides and interpret the slides. The supervisors dispatched from vector borne and NTD control (VCD) division of ministry of health of Uganda will join the prevalence survey of 2021. The supervisors will examine at least 10% of slides which were already examined by the group of professors and the health specialist to ensure the accuracy of the prevalence survey. The results of the parasitological examination will be recorded in the case report form.

Alternatively, if South Korean professors are not permitted to travel due to an international travel ban because of the COVID-19 pandemic, the MANE team would request VCD in advance to form the study team composed of laboratory technicians belonging to Uganda's ministry of health or the Eastern regional authority of Uganda.

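### Open-label allocation in a disclosed fixed block of 8, with no provision in the available text for concealing the lists or masking the day-21 slide readers

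*Protocol*

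**What the plan says.** On allocation, Protocol section 3.4 is explicit about the mechanics:

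- Design: "The trial is designed as an open-label randomised controlled trial with four arms". Two arms receive avocado, and the two dual-dose arms come back on the next day, so the arm is evident to those present.
- Method: children are allocated "by applying the block randomisation method, stratified by health facility". "A randomisation list will be prepared beforehand using a random number generator".
- Block: "The randomisation block size will be 8, and within each block there will be two participants allocated to each of the four trial arms".
- Lists: "Each health facility will have its own random number list".
- Staff: "The field researchers will be formed by health personnel from the most accessible health centre IV or hospital-level health facility in Mayuge district". Four such facilities are named, Kigandalo health centre IV among them.

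On outcome reading, section 3.5.2 says that "Kigandalo health centre IV will be the base for parasitological examination". Section 3.5.4 gives the reading of Kato-Katz slides to six external professors of parasitology together with "the health specialist of Mayuge NTD Elimination project, will examine the prepared slides and interpret the slides". Ministry or regional laboratory technicians are the fallback. Supervisors re-read at least 10% of slides, a check written for the prevalence survey and not stated to be blind. Section 3.4 speaks of the project team finding day-21 positives. Section 3.7.1 makes cure rate and egg reduction rate the primary outcomes, and both come from these slides.

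The available text names no custodian for the lists, no envelope or central release, no coded labels and no masking of readers.

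**The concern.** Two safeguards matter most when treatment cannot be blinded: the next assignment should not be foreseeable, and whoever measures the outcome should not know the arm. Here the first is weakened by what section 3.4 states, and the available text provides for neither.

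**Allocation.** The Introduction (paragraph on infection intensity) says that cure rates fall when the pre-treatment egg count is high. Figure 1 places the egg counts before the split into arms, and section 3.4 randomises only children already found positive, so a strong predictor of cure exists before allocation. At the planned 12% prevalence and 50 children per school (section 3.6.1), about 0.12 × 50 = 6 positive children would attend at a school, and no rule fixes their order. If the next assignment can be foreseen, the order of presentation can be chosen. The cure comparison in section 3.7.1 is an unadjusted chi-square test, which would not correct a resulting imbalance.

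**Reading.** A slide holds 41.7 mg and each egg counts as 24 eggs per gram (section 3.7.1). If cure means that no eggs are seen, one egg found or overlooked reverses the result. A reader who knows the arm may search a near-negative slide more or less hard. The trial cited for the power assumption (reference 42) calls itself assessor-blind in its title, so masked reading looks feasible for this kind of endpoint.

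**Working it through.** **Inputs.** Block of 8 with two per arm (3.4); total 196, and 93 per comparison group for 70% versus 50% at 80% power and 5% type I error (3.6.1).

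**1. The plan's own figure.** Two proportions, two-sided 5%, no continuity correction:

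n = [1.96 × √(2 × 0.6 × 0.4) + 0.8416 × √(0.5 × 0.5 + 0.7 × 0.3)]² / 0.20² = (1.358 + 0.571)² / 0.04 = 93.

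The total is 186, and 186 / 0.95 = 195.8, so 196. The figure reproduces and is not in dispute.

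**2. Assignments known with certainty.** Take someone who knows the block size and has seen the earlier assignments.

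- Position 8 is always certain.
- Position 7 is certain when the last two places belong to the same arm. Given the arm in place 7, its partner is equally likely to be in any of the other 7 places, so the probability is 1/7.
- Positions 1 to 6 are never certain.

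Share = (1 + 1/7) / 8 = 1/7 = 14.3%; 196 / 7 = 28.

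If the 196 split evenly over four facilities (an assumption), each has 49: six full blocks and one child over. Then 6 × 8/7 = 6.86 of 49, or 14.0%, about 27 in all. With the 212 children of Figure 1, 212 / 7 is about 30.

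**3. Dose alone.** Each block has four dual-dose and four single-dose places. The expected length of the final run of one dose is 1 + 3/7 + (3/7)(2/6) + (3/7)(2/6)(1/5) = 1.6, and 1.6 / 8 = 20% certain.

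**4. Best guess.** Over all 8! / (2!)⁴ = 2,520 possible block sequences, always guessing the arm with most places left is right 47% of the time, against 25% by chance. For dose alone it is 67%, against 50%.

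**5. Varied blocks.** Simulation with 49 children per facility and a guesser who knows the set of sizes but not their order (the sizes are assumptions):

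| Block sizes | Certain | Best guess right |
| --- | --- | --- |
| 8 fixed | 14.0% | 47% |
| 4, 8 | 7.0% | 48% |
| 8, 12 | 4.3% | 44% |
| 4, 8, 12 | 3.2% | 46% |
| 8, 12, 16 | 2.2% | 43% |

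Varied blocks sharply cut the certain assignments but hardly change the best guess. None of this helps if the list itself can be seen.

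**6. What arm-dependent reading could do.** This is illustration only, because the protocol gives no misreading rate. Suppose true cure is 50% in both groups of 93, and a share m of true positives is called negative in one group only. The false difference is 0.5m. For m = 10%, the apparent rates are 50% and 55%. The standard error is 0.0732 under the null and 0.0731 under the alternative, so the chance of a significant result is P(Z > (1.96 × 0.0732 − 0.05) / 0.0731) plus the small lower tail, 0.1005 + 0.0041 = 10.5%.

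| Assumed m | False difference | Type I error |
| --- | --- | --- |
| 0 | 0 points | 5.0% |
| 5% | 2.5 points | 6.3% |
| 10% | 5 points | 10.5% |
| 20% | 10 points | 27.7% |

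Only the day-21 slides are exposed to this, since baseline slides are read before randomisation.

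**The case against.** The strongest reply is that no route to bias is demonstrated, and several tempting inferences go beyond the text.

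- *A reader might infer that unmasked project staff read the slides.* The protocol does not say so. Most named readers are external professors, with one project specialist, and the fallback is ministry or regional technicians. Nothing says that the arm appears on containers, slides or forms. A laboratory at one of the four facilities does not unmask anyone by itself, and nobody is shown both to allocate and to read. A short stretch of text before section 3.5.1 was also unavailable, which makes silence weaker evidence.
- *A reader might infer that each facility holds and sees its list.* The sentence follows the one on stratification and may mean only one list per stratum.
- *A reader might infer that both biases favour dual dose and avocado.* For allocation the direction is unknown. Steering heavily infected children to dual dose would lower that arm's cure rate.
- *Scope.* Consent to the trial is given together with consent to the survey (3.2), so foresight would mainly affect the order of presentation, not who qualifies.

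All of this stands, and it limits the claim. It does not supply the missing safeguards: the block size is fixed and disclosed, facility personnel run the visits, and the available text provides for neither concealment nor masked reading. These are matters of trial conduct that belong in the protocol, not details to leave to an analysis plan.

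**Conclusion.** The point holds as a cheap improvement to the design, not as evidence that the results will be biased. With a fixed, disclosed block of 8, 14.3% of assignments (about 28 of 196) are certain in advance to anyone who tracks them, 20% if only the dose matters, and all of them if the list is visible. This assumes that the tracker knows the block size, which is printed in the protocol, and sees the assignments at that facility, which the open-label design makes easy.

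These figures measure predictability. The bias in cure rate that could follow is unknown in size, and for allocation also in direction. The type I error figures rest wholly on assumed misreading rates and show only what is possible. The documents do not support the stronger statements that the readers are unmasked, that the lists are held by the facilities, or that varied blocks would remove the problem.

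**What to change.** 1. **Mask the day-21 reading.** Label containers and slides with a study ID only, one that does not encode the arm or the place on the list. Keep the allocation list from the Kigandalo laboratory. Describe the trial as open-label with masked slide readers. Results can be linked back to the child through the ID after reading.
2. **Conceal allocation.** Have the list held by an existing team member who takes no part in enrolment or slide reading. Release assignments in sequence from sealed, opaque, numbered envelopes, one series per facility.
3. **Vary the blocks.** Replace the fixed 8 by randomly varied sizes, for example 4, 8 and 12, and do not disclose them to site staff. This reduces certain assignments to about 3% but does not remove predictability, so it supplements concealment and does not replace it.

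The cost is relabelling, a set of envelopes and a new computer-generated list, with slightly more handling of IDs and envelopes in the field. Sample size, arms and visits stay as they are. The change must be made before the first child is randomised.

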**3.5.1 Questionnaire survey**

Trained field workers will administer pre-tested questionnaires to enrolled participants, entering data on tablet PCs. The questionnaire includes sections on: 1) demographic information, 2) general sanitation and hygiene conditions, 3) contact with contaminated water and soil, 4) contact with animals, 5) their habits to use water and life styles.

**3.5.2 Stool sample collections**

Stool samples will be collected from enrolled students from the selected schools by the field workers who will visit the schools, and, as described above, from the students who take part in the albendazole treatment trial three weeks after treatment. The collected stool samples will be contained in a designated stool container secured in a cooling box carried by the field workers. The samples will be transferred to the laboratory and the Kato-Katz examination performed. Delivered stool containers will be secured in a refrigerator before being processed, and contained stools will be utilized for making slides with Kato-Katz method within 24 hours after being delivered to the laboratory.

- - 1. **Organizing laboratory examination**

The WHO recommends the Kato-Katz quantitative method as the standard methods for evaluating prevalence and intensity of soil-transmitted helminthiasis and schistosomiasis in endemic communities. Kigandalo health centre IV will be the base for parasitological examination since this health centre IV has the central laboratory of Mayuge district.

(Collection of stool samples)

Plastic stool containers and applicator sticks are provided in advance

1. Put stool (about 5g) into a plastic container.

2. Take stool to the school.

3. Keep stool in the container in the cooler boxes.

4. The cooler boxes contained stool samples are transported to Kigandolo HC IV for analysis in the afternoon of the same day.

5. Stool samples which are not treated with Kato-Katz method will be contained a refrigerator in the Kigandalo HC IV.

**3.5.4 Parasitological examination for STH and schistosomiasis**

Kato-Katz procedure will be applied to prepare the slide for examination. Six South Korean professors of parasitology who participated in the prevalence survey in 2019 and the health specialist of Mayuge NTD Elimination project, will examine the prepared slides and interpret the slides. The supervisors dispatched from vector borne and NTD control (VCD) division of ministry of health of Uganda will join the prevalence survey of 2021. The supervisors will examine at least 10% of slides which were already examined by the group of professors and the health specialist to ensure the accuracy of the prevalence survey. The results of the parasitological examination will be recorded in the case report form.

Alternatively, if South Korean professors are not permitted to travel due to an international travel ban because of the COVID-19 pandemic, the MANE team would request VCD in advance to form the study team composed of laboratory technicians belonging to Uganda's ministry of health or the Eastern regional authority of Uganda.

## 3.6 Sample size and sampling method

**3.6.1 Sample size**

**For phase I:**

Sample size determination for the prevalence survey will be based on the comparison of prevalence of schistosomiasis and soil-transmitted helminths in Mayuge district in 2019 with the anticipated prevalence of STH and schistosomiasis after two years’ project implementation.

The baseline prevalence of STHs in 2019 was 15.8 % and it is anticipated that MANE program activities will reduce the prevalence of STHs to 12% by the time of the 2021 survey. For schistosomiasis, the prevalence was 27.2% in 2019, and it is estimated that MANE program activities will reduce schistosomiasis prevalence to 18% by the time of the 2021 survey.

Applying to the difference of expecting prevalence of STH in 2021 and proven prevalence of STHs in 2019, a target sample size for the 2021 prevalence survey of 1300 participants would be required for 80% power to detect a difference between 2019 and 2021 STH prevalence at 5% significance level.

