2) Integrating NTD services within the broader health care delivery system.

3) Strengthening advocacy to increase the portion of domestic funding for NTD from 12% to 25% by 2025.

4) Identification indicators for monitoring the progress on NTD programs.

- - 1. **Mayuge NTDs Elimination (MANE) project**

World Vision, funded by Korea International Cooperation Agency (KOICA), has implemented comprehensive NTD elimination programs targeting STHs and schistosomiasis in Mayuge district since 2019, known as the Mayuge NTDs Elimination (MANE) project. The MANE project is a three-year program composed mainly of mass drug administration (MDA), water, sanitation and hygiene (WASH), and awareness increasing programs for the communities and health workers. For the WASH component, of 13 sub-counties of Mayuge district, two sub-counties covering 25,000 population will benefit from the piped water system. The MANE project has been constructing constructs nineteen public latrines in selected schools and implemented community-led total sanitation (CLTS) programs in 25 villages. For increasing awareness program, the MANE project has utilised a citizen voice and action (CVA) program developed by World Vision to improve people’s awareness of their public health issues and strengthen the relationship between the community and the authorities.

In 2019, a prevalence survey was done as the baseline survey to understand the burden of STH and schistosomiasis in Mayuge district. According to the WHO guideline, the MANE team selected the samples from 1,123 9-10 years old children who are equivalent to P4 and P5 grade students in the Ugandan education system (13). Baseline prevalence of schistosomiasis was 27.2% (305/1,123) and prevalence of STH was 15.8% (177/1,123). Among the 177 identified STHs positive samples, 96% (n=170) of STHs were hookworms.

- - 1. **Hookworm dominance in the prevalence of STH**

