**21 days later after treatment**

**(5% follow up loss)**

**Cure rate and egg reduction rate will evaluated**

## 3.3 Sampling method for prevalence survey

**3.3.1 Selection of schools**

Of 504 schools in Mayuge district, 33 schools will be selected randomly and independently from the school list stratified by the parish and sub-county using probability proportional to size selection (PPS). Before the sample selection, the sampling frame will be sorted within each sampling stratum first, by size. The required number of schools shall then be selected by probability proportional to size (PPS).

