**For phase II:**

For the trial phase of the study, the aim is to assess the effect of co-administration with fatty foods, and of dual-dose versus single-dose albendazole on hookworm cure rate. The cure rate of single dose albendazole for hookworms varies between 36% and 93% in previously reported studies. Based on data from Adegnika et al (42), we power our trial to detect a difference in cure rate of 70% versus 50% for both co-administration with fatty foods versus no co-administration, and for dual-dose versus single-dose albendazole.

With type I error probability of 5%, 93 participants in each comparison group will be required for 80% power to detect a difference in cure rate of 70% versus 50%. Therefore, the total target sample size for the trial will be 186. However, allowing for 5% loss to follow-up, i.e. 5% of hookworm positive cases not appearing on the follow up stool test 21 days after treatment, the target sample size will increase to 196. If the expecting prevalence of hookworm in 2021 is 12%, to satisfy the sample size of 196, the target sample size of the prevalence survey of 2021 will be 1,634. Therefore, a total sample size of 1,650 will be sufficient to cover sample size requirements of both the prevalence survey and the nested trial.

Assuming that 50 children will be selected from each school, a total of 33 schools will be randomly selected in order to achieve the required sample size.

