**3.7.1 Data analysis**

The MANE team will use Open data kit (ODK) of World Vision for data generation, collection and store

1. ODK build: pre-tested questionnaire questions will be transferred into ODK format.
2. ODK collect: pre-trained field workers will collect data from the participants during the prevalence survey
3. ODK aggregate: collected data will be uploaded and stored into World Vision ODK server.

Data saved in the ODK system will be exported into Microsoft Office Excel, and the data will be checked errors, any missing values, and extreme values. The cleaned data will be exported to the statistic program (Stata or R).

Prevalence of STHs and schistosomiasis with 95% confidence intervals will be calculated. The arithmetic eggs count will be obtained from the microscopic examination of the Kato-Katz method applying made slide. A multiplication factor of 24 should be applied to calculate eggs per gram, since the stool quantity in a slide prepared with the Kato-Katz method contains 41.7mg of the stool. The intensity of infection will be categorised by the criteria of WHO guideline as below(13).

|  | Light intensity infections | Moderate intensity infections | Heavy intensity infections |
| --- | --- | --- | --- |
| *A. lumbricoides* | 1-4,999 epg | 5,000-49,999 epg | ≥ 50,000 epg |
| *T.trichiura* | 1-999 epg | 1,000-9,999 epg | ≥ 10,000 epg |
| Hookworm | 1-1,999 epg | 2,000-3,999 epg | ≥ 4,000 epg |
| *S.mansoni* | 1-99 epg | 100-399 epg | ≥ 400 epg |

(Table 2) The threshold of infection intensity by each STH and *S.mansoni*

I will analyse the relationship between the prevalence and the risk factors from the questionnaire survey. Chi-square (χ2) test or Fisher’s exact test will be applied to assess categorical variables on the prevalence of STHs and schistosomiasis. χ2 Test for trend will be used for evaluating ordered categorical variables on the prevalence of STHs and schistosomiasis. The univariate analysis will be carried out to identify the association between potential risk factors and prevalence. I will conduct multivariate logistic regression analysis to determine which risk factors are associated with the outcomes of the prevalence of STHs and schistosomiasis, with the risk factors significantly (p-value < 0.05) associated with hookworm and schistosomiasis infection.

Continuous variables such as eggs counts for the dependent variable will be assessed by using t-test.

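### The phase I survey claims 80% power for the STH comparison with no design effect, although it samples whole classes from 33 schools; any appreciable between-school correlation takes power below 80%

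*Protocol*

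**What the plan says.** Section 3.6.1 of the protocol (phase I) sizes the 2021 survey on a comparison with 2019. The inputs are "The baseline prevalence of STHs in 2019 was 15.8" percent and an expectation that the programme will "reduce the prevalence of STHs to 12% by the time of the 2021 survey". The conclusion is that "a target sample size for the 2021 prevalence survey of 1300 participants would be required for 80% power", with the test set at the 5% level. The paragraph mentions neither the size of the 2019 sample nor a design effect.

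The 2019 size is in the Introduction, in the part on the MANE project: "the MANE team selected the samples from 1,123 9-10 years old children", of whom 177 (15.8%) had an STH.

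The sampling plan is clustered. Under 3.3.1, "33 schools will be selected randomly and independently from the school list", stratified by parish and sub-county and with probability proportional to size. Under 3.3.2, one class of 40 to 50 is drawn in each school, and a second class is added if fewer than 35 children are present. Section 3.6.1 (phase II) raises the total to 1,650 to find enough hookworm cases for the trial, describes that total as sufficient for the survey as well, and converts it to schools: "Assuming that 50 children will be selected from each school, a total of 33 schools will be randomly selected".

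For analysis, section 3.7.1 says "Prevalence of STHs and schistosomiasis with 95% confidence intervals will be calculated". It names chi-square, Fisher and trend tests and logistic regression for prevalence and risk factors. It mentions no school term, sampling weight or cluster-robust variance.

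**The concern.** Children in the same class share water sources, sanitation, soil and treatment history, so their infection status is likely to be correlated. A sample of 33 classes then carries less information than the same number of children drawn independently. The protocol itself expects schools to differ: the fallback in section 3.6.1 for too few trial participants is to return to schools with high hookworm prevalence.

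Two things are at stake. Evaluating the MANE project's effect on STH and schistosomiasis is a stated aim (section 2). If STH power is well below 80%, a non-significant change could be misread as no effect. In addition, intervals and tests that treat children as independent overstate precision. This bears on the prevalence estimates and on specific objective iii, the risk-factor analysis.

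**Working it through.** **Inputs.** From the protocol: p1 = 0.158, p2 = 0.12, 5% level, 80% power, 2021 target 1,300 (section 3.6.1, phase I); n1 = 1,123 in 2019 (Introduction); planned n2 = 1,650, with 33 schools of 50 (section 3.6.1, phase II). Assumed: a two-sided test, since sidedness is not stated, and the ICC, which the protocol does not give.

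**Step 1: reproduce 1,300.** For two equal independent groups with pooled variance under the null, the mean prevalence is 0.139 and

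n per group = [1.960 × √(2 × 0.139 × 0.861) + 0.8416 × √(0.158 × 0.842 + 0.12 × 0.88)]² / 0.038² = (0.9589 + 0.4111)² / 0.001444 ≈ 1,300.

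The match is exact. A one-sided test gives 1,024, a continuity correction 1,352, and a one-sample test against a fixed 15.8% gives 677. The stated figure therefore implies 1,300 children in 2019 too, and a design effect of 1.

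**Step 2: use the real 2019 size, children still independent.** Power = Φ[(0.038 − 1.960 × SE0) / SE1], where SE0 is the pooled and SE1 the unpooled standard error.

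- 1,123 v 1,300: SE0 = 0.01403, SE1 = 0.01413, power 77.1%. Reaching 80% would take 1,518 in 2021.
- 1,123 v 1,650: SE0 = 0.01324, SE1 = 0.01351, power 81.4%.

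The planned 1,650 exceeds 1,518, so the 2019 size does no harm on its own.

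**Step 3: allow for clustering.** Design effect DE = 1 + (50 − 1) × ICC. Sample sizes are divided by DE, either in both surveys or in 2021 only, because the protocol does not say how the 2019 sample was drawn. The half-width is 1.96 × √(0.12 × 0.88 × DE / 1,650).

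| ICC (assumed) | DE | STH power, both clustered | STH power, 2021 only | Schistosomiasis power (27.2% v 18%), both clustered | 95% CI half-width around 12% |
|---|---|---|---|---|---|
| 0 | 1.00 | 81% | 81% | – | 1.6 points |
| 0.01 | 1.49 | 65% | 74% | 99.7% | 1.9 |
| 0.02 | 1.98 | 53% | 67% | 98% | 2.2 |
| 0.05 | 3.45 | 34% | 50% | 87% | 2.9 |
| 0.10 | 5.90 | 22% | 35% | 66% | 3.8 |

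STH power drops below 80% at DE of about 1.038 if both surveys are clustered (ICC 0.038/49 ≈ 0.0008), or about 1.088 if only 2021 is (ICC 0.088/49 ≈ 0.0018). With 40 children per school and the total held at 1,650, STH power with both clustered still runs from 68% at ICC 0.01 to 26% at 0.10.

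**Step 4: risk-factor tests.** An unadjusted 5% test has a true error rate of about 2 × [1 − Φ(1.96/√D)], where D is the variance inflation for that exposure. For an exposure identical for every child in a school, D = DE, which gives 11%, 16%, 29% and 42% at the four ICCs. For an exposure that varies between children, D is roughly 1 + 49 × ICC(outcome) × ICC(exposure). With an assumed exposure ICC of 0.10, the rates are about 6%, 6%, 8% and 11%.

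**The case against.** **The 2019 sample size.** A reader might infer that using 1,300 instead of 1,123 leaves the survey short. It does not: 1,650 are planned, giving 81.4% under independence. This objection stands in full.

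**Error rate of the 2019–2021 test.** A reader might infer that the protocol's test of the time change has a false-positive rate of 11% to 42%. The protocol does not support that, because section 3.7.1 names no test for that contrast and no interval formula. Nor do those rates apply to all risk factors. Most questionnaire items in section 3.5.1 are answered child by child, and inflation is much smaller where answers vary within a school.

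**Size of the loss.** No ICC is given, and the 2019 sampling method is not described. Stratification may recover a little precision. The power figures are therefore conditional, and the case with only 2021 clustered belongs beside the harsher one.

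**Schistosomiasis.** It would be wrong to say that the whole 2019–2021 comparison is underpowered. Schistosomiasis stays above 80% up to ICC 0.05 even with both surveys clustered.

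**Scope.** Section 3.2 calls phase I descriptive, and the time contrast is not among the specific objectives in 2.2. Weights and variance methods are often left to an analysis plan, which is not at hand. An analysis plan could settle how the data are analysed. It could not make correct a power statement, or a claim that 1,650 is sufficient, that allows nothing for clustering.

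**Conclusion.** The point holds for the phase I power statement on STH. The 1,300 is computed correctly, but for a design the survey does not have. The 80% claim, and the description of 1,650 as sufficient for the survey, fail at any ICC above about 0.001 to 0.002. How far power falls depends on the assumed ICC and on whether 2019 was also clustered; the plausible span is wide, from 74% down to 22%.

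On analysis the conclusion is narrower. Followed as written, the prevalence tests and logistic regression carry no school term and understate error, most for exposures shared within a school and little for those that vary between children in the same school. A simple binomial interval would be too narrow by a factor of √DE, which is 1.22 to 2.43 over the range shown. The individually randomised trial's sample size is not touched.

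**What to change.** 1. In section 3.6.1 (phase I), restate STH power for 1,650 v 1,123 with a design effect. Estimate the between-school ICC from the 2019 data if school was recorded; otherwise show power over a range of ICCs. State how the 2019 sample was drawn, and amend the statement that 1,650 is sufficient for the survey.
2. In section 3.7.1, or in an analysis plan to which it refers, specify school as the primary sampling unit, the sampling strata, and selection weights that reflect the class selection and the second-class rule. Report design-based confidence intervals and Rao-Scott tests.
3. Use cluster-robust or school random-effect logistic models for the risk factors and for the 2019–2021 contrast.

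The cost is wording plus standard survey commands in Stata or R, which the protocol already names. No extra children are needed for these changes. They do not restore the lost power: the stated power will be less favourable and the intervals wider.
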